## Abstract

**Background:**

Adolescent social anxiety disorder (SAD) is common, impairing and persistent. There is a need to intervene early to avert its long-term consequences. Cognitive Therapy for SAD is the leading treatment for adults and shows promise for adolescents. However, given the scale of the problem of adolescent SAD and the limited availability of psychological therapists in child and adolescent mental health services, there is a substantial gap in service provision. Delivering therapy via the Internet may provide part of the solution to this problem. An Internet version of adult Cognitive Therapy for SAD has been developed, with outcomes similar to face-to-face therapy. We have recently adapted this treatment for use with adolescents with SAD. Here, we describe a randomised controlled trial designed to test the efficacy of Internet Cognitive Therapy for adolescent SAD compared to waitlist.

**Methods/design:**

Forty adolescents aged 14–18 years with a diagnosis of SAD will be recruited via schools. Participants will be randomly allocated to Internet Cognitive Therapy or to waitlist. All participants will be assessed three times during the study—at baseline (pretreatment/wait), midtreatment/wait (week 8) and posttreatment/wait (week 15). Participants in the experimental arm will also complete weekly measures as part of the online program and they will be assessed at 3 and 6 months. Postwait, participants in the waitlist arm will be offered Internet Cognitive Therapy, and weekly and posttreatment data will also be collected for them. The trial aims to test whether Internet Cognitive Therapy is superior to waitlist in reducing social anxiety symptoms and in reducing the proportion of adolescents meeting criteria for SAD. Other outcomes of interest include depression and general anxiety symptoms. Acceptability of the online treatment will also be evaluated.

**Discussion:**

This randomised controlled trial will provide preliminary evidence on whether this intervention, requiring relatively low levels of therapist input, is safe and clinically effective. If this is shown to be the case, Internet Cognitive Therapy for adolescents has the potential to provide a service to the large population of adolescents with untreated SAD.

**Trial registration:**

ISRCTN Registry, ISRCTN15079139. Version 1 registered on 06/02/2019.

**Electronic supplementary material:**

The online version of this article (10.1186/s13063-019-3651-6) contains supplementary material, which is available to authorized users.

## Background

Social anxiety disorder (SAD) is the third most common mental health disorder [1], with prevalence rates estimated to be as high as 10% by the end of adolescence [2]. Almost all cases of SAD occur during the adolescent years [1]. It is associated with substantial impairment in relationships [3], educational attainment [4], and day-to-day functioning, as well as an elevated risk of further anxiety and depressive disorders [5]. For the majority of sufferers, the disorder is characterised by a persistent course [6, 7]. Intervening in the early stages of SAD has the potential to offset the multiple, negative consequences associated with the disorder.

Currently the most common psychological treatment approach for adolescents with SAD is generic forms of cognitive behaviour therapy (CBT) developed for a range of anxiety disorders. Unfortunately, young people with SAD have significantly poorer outcomes from these treatments compared to those with other anxiety disorders [8–13]. For example, for 7–17 year olds, remission from SAD was 40.6% compared to 72% for separation disorder or generalised anxiety disorder [9]. Disorder-specific psychological therapies (e.g. [14–16]) have been shown to outperform waitlist but there is limited evidence of specific treatment effects, in the sense of being superior to other credible interventions. In contrast, for *adults* with SAD, a form of individual psychological therapy, Cognitive Therapy based on the Clark and Wells [17] cognitive model, has been shown to be more effective than a wide range of alternative therapies in a network meta-analysis (Mayo-Wilson et al., [18]) and is one of the first-line treatments recommended by the National Institute for Health and Care Excellence (NICE, [19]). Turning to young people, the NICE guideline recommends that the use of Cognitive Therapy should be considered for older adolescents with SAD. In line with this, we have demonstrated promising findings in a case series (Leigh & Clark, [20]) in which we adapted Cognitive Therapy for adolescents. Furthermore, Ingul et al.([21] undertook a randomised controlled trial (RCT) comparing individual therapy based on the Clark and Wells cognitive model [17] to group CBT [22] and an attention placebo. Even though the individual therapy provided in the trial was an attenuated form of Cognitive Therapy for SAD, it was found to outperform both comparator conditions, providing preliminary evidence of specific treatment effects. Taken together, it seems that Cognitive Therapy based on the Clark and Wells model may hold promise as an effective treatment for adolescent SAD [23].

Whilst there are encouraging advances in treatment development for adolescent SAD, there are major obstacles to treatment access and service provision. Most young people with mental health disorders do not receive any treatment and the treatment gap is particularly large for youth with anxiety disorders [24]. For example, the US National Comorbidity Survey reported that less than one in five adolescents received services for an anxiety disorder, and only 12% of young people with SAD received any treatment, rising to 21% amongst those with severe SAD [24]. Even for those who do access treatment, the majority do not receive an adequate, evidence-based intervention [25]. There are many reasons for the unmet need. These include parent and child level factors, such as stigma, lack of awareness and low trust in professionals [26], and also service level factors, including failure to detect SAD by primary care professionals, limited resources of Child and Adolescent Mental Health Services (CAMHS), leading to long waiting times, and a limited number of trained therapists [27].

There is clearly a need to develop effective, scalable treatments in order to bridge the treatment gap that exists for the majority of adolescents with SAD. One potential solution to the problem of limited access is the use of the Internet to deliver therapy. Potential benefits to services of Internet-delivered therapy include reduced therapist time and reduced burden on clinics, for example, by lowering the need for clinic space. There are also a number of potential advantages of Internet therapy to young service users and their families. Internet therapy may be more convenient because young people can use the treatment programme when it suits them. Travel time and costs for attending sessions are minimised. The disruption to schooling caused by therapy sessions, typically scheduled during working hours, is also almost eliminated. Young people interact with the online environment in all aspects of their lives and so receiving treatment this way may be especially appealing to this cohort. Accessing a treatment online may provide a greater sense of confidentiality and reduced embarrassment [28] which will be especially important for adolescents with social anxiety for whom feelings of shame and embarrassment are typical [29].

Our team have developed and tested an Internet version of Cognitive Therapy for SAD for *adults*. Therapist contact is all remote (email, text, phone) and therapist time is reduced to only 20% of that in face-to-face therapy [30]. A recent RCT with socially anxious adults found that the Internet therapy has similar effects to face-to-face Cognitive Therapy (Clark et al., in preparation). We have recently undertaken a consultation study with young people to identify how this adult Internet treatment needs to be adapted to meet the needs of an adolescent SAD population. Only minor adaptations were suggested, for example ensuring that case examples are relevant to young people (e.g. describing adolescent-relevant situations, such as being at school and seeing friends, rather than being at work).

The primary aim of this Online Social anxiety Cognitive therapy for Adolescents (OSCA) trial is to examine the effectiveness of Internet Cognitive Therapy for adolescents with SAD compared to waitlist within a school setting.

We hypothesise that treatment with OSCA will be superior to waitlist in reducing symptoms of social anxiety and that the proportion of adolescents meeting criteria for social anxiety disorder will be lower posttreatment compared to postwait. We hypothesise that gains will be maintained at 3- and 6-month follow-up. We also expect that treatment with OSCA will be superior to waitlist in reducing symptoms of general anxiety and depression. We will gather data on the acceptability of the treatment. We will also examine whether proposed psychological process variables mediate any observed change in social anxiety symptoms after OSCA, and whether we can predict who will benefit in particular from OSCA. The results of the present clinical trial will be used to improve access to effective psychological treatments for socially anxious adolescents.

## Methods/design

### Design

The study is a two-arm RCT conducted in secondary schools in the United Kingdom (UK). The experimental arm is Online Social anxiety Cognitive therapy for Adolescents (OSCA). The comparison arm is waitlist. All participants will be assessed three times: at baseline (pretreatment/wait), midtreatment/wait (week 8) and posttreatment/wait (week 15). Participants in the experimental arm will also be assessed at 3- and 6-month follow-up. Postwait, participants in the waitlist arm will be offered OSCA. Assessments will be undertaken with parents as well where possible. Figure 1 shows the trial flow diagram. The trial has received approval from the University of Oxford Medical Sciences Division Research Board and it has been prospectively registered (http://www.isrctn.com/ISRCTN15079139).

**Fig. 1 Fig1:**
[figure not shown]
OSCA trial flowchart

The basic trial methods of enrolment, interventions, and assessments are summarised in Fig. 2. The Standard Protocol Items: Recommendations for Interventional Trials (SPIRIT) checklist is provided as Additional file 1.

**Fig. 2 Fig2:**
[figure not shown]
SPIRIT figure for OSCA trial

### Participants

A total of 40 adolescents aged between 14 and 18 years at intake with a diagnosis of SAD will be included. Diagnostic and Statistical Manual of Mental Disorders, 5th edition (DSM-5) diagnosis will be determined by the Anxiety Disorders Interview Schedule for children and parents [31]. Only adolescents for whom SAD is the primary problem will be included. All participants must be able to read and write in English due to the nature of the therapy and the need to complete self-report questionnaires.

Young people who are currently receiving any other psychological intervention or who have previously received Cognitive Therapy or CBT for SAD will not be invited to take part. Other exclusion criteria include: the presence of an autism spectrum disorder; learning disability; current alcohol or substance dependence; presence or suspected presence of psychosis; suicidal intent or recurrent self-harming behaviour; and young people identified by social services as currently ‘at risk’ due to child protection concerns.

### Sample size

Sample size was estimated from an RCT of adolescents with SAD comparing a version of face-to-face Cognitive Therapy with attention placebo (Ingul, Aune, & Nordahl, 2014). The comparison effect size posttreatment was 1.26. A recent adult RCT by our group suggests outcomes for face-to-face and Internet-delivered Cognitive Therapy are similar. Based on a conservative estimate of the effect of 1.0, we would need 17 per group for 80% power. The sample size was inflated to allow for drop out following randomisation [32], resulting in a final sample size of 40.

### Recruitment and randomisation

Participants will be recruited via secondary schools. The use of schools as a referral source has two advantages. It will ensure adolescents with a range of symptom severity will be included and it fits with potential future delivery mechanisms for the treatment, should efficacy be demonstrated.

For the screening stage, during class time in school, young people will be asked to complete the Mini-SPIN [33] and to indicate whether or not they would like to learn more about the study. The Mini-SPIN is a three-item questionnaire that is sensitive and specific to SAD in adults [34] and adolescents [35]. We were guided in how best to recruit participants in a non-stigmatising way in consultation with school students. Prior to initiating recruitment in schools we will send information out to parents informing them of the project and providing details of what will be happening in their child’s school.

The process of seeking informed consent will differ for 14 to 15 year olds and 16 to 18 year olds. This is because 16 to 18 year olds will be treated as ‘competent youth’ for the purposes of this study. For 14 to 15 year olds, information about the study will be provided to the young person after parental consent has been obtained. For 16–18 year olds, information about the study will be provided to the young person directly, without seeking parental consent first. At least 24 h after information has been given to the young person, a meeting will be scheduled during school hours. At this meeting written assent/consent will be sought. Once written assent/consent has been obtained, the full pre-intervention assessment will be completed. This will involve ensuring all eligibility criteria are met. For 16–18 year olds, we will also seek their agreement to contact parents in order to inform them of their child’s involvement in the project.

Adolescents meeting inclusion criteria and not meeting any exclusion criteria will be randomised to waitlist or treatment. Adolescents not eligible to take part after the parent and young person assessments will be supported in accessing help via alternative means (if they would like this). Eligible participants will be randomly allocated to OSCA or waitlist. Individual randomisation will be conducted using an online minimisation algorithm generated by the trial statistician. The ratio will be 1:1. Minimisation will ensure balance between trial arms for gender, but will retain a random element and will be stratified by severity. Randomisation will occur after consent has been taken and baseline measures have been completed. It will be done by the Oxford Cognitive Health and Neuroscience Clinical Trials Unit. The trial team will email details of the stratification variables to the independent statistician who will then randomise the participant. Following randomisation, participants will be notified of their allocation.

### Outcomes

#### Primary outcome measures

The primary outcomes will be changes on the self-report version of the Liebowitz Social Anxiety Scale for Children and Adolescents–Self-report Version (LSAS-CA-SR) [37], and recovery from SAD. To assess recovery, the proportion of adolescents who continue to meet DSM-5 diagnostic criteria for SAD at posttreatment/wait will be examined. Diagnosis will be made using The Anxiety Disorders Interview Schedule IV for Children and Parents (ADIS-C/P) [31]. All participants will be interviewed with the child version and parents will be interviewed where possible. Participants who withdraw from the study will also be invited to complete the assessments. Assessments will be completed face-to-face or over the telephone by trained assessors. See Table 1 for timings of outcome measures.

**Table 1 Tab1:**
[figure not shown]
Schedule of self-, parent- and therapist-report measures

#### Secondary outcome measures

As secondary outcomes, changes on a measure of aspects of social anxiety (the Social Phobia Weekly Summary Scale [38]), general anxiety as measured by the Revised Child Anxiety & Depression Scale (RCADS, self-report [and parent report where possible]) [39] and depression as measured with the Short Mood and Feelings Questionnaire (SMFQ) [40] will be examined. Social functioning (including social satisfaction, friendship quality and peer victimization) will be assessed by self-report questionnaire and school functioning will be captured through percentage attendance and grade average (either internal or external examination scores or grade estimate). Self-reported ability to concentrate in class will be measured [20]. See Table 1 for timings of outcome measures.

The following measures of possible mediators of therapeutic improvement will be used: the Adolescent Social Cognitions Questionnaire (ASCQ); Adolescent Social Behaviours Questionnaire (ASBQ); and Adolescent Social Attitudes Questionnaire (ASAQ). These three measures were all adapted for adolescents by the authors from versions developed for socially anxious adults [38].

#### Measure of alliance and treatment credibility and acceptability

The quality of the therapeutic relationship, as perceived by both the therapist and the participants, will be assessed with the shortened Working Alliance Inventory [41] as a potential predictor of outcome. Participants will rate treatment credibility with the Credibility of Therapy Scale [42] as another potential predictor of outcome. Feedback questionnaires will be completed posttreatment to assess the acceptability of the treatment.

### Blinding

Blinding of therapists and participants is not possible due to the nature of the design. However, assessments will be carried out by independent raters who are blind to allocation. The independent raters will be psychology graduates or above. All will have received training in the use of the outcome assessment. All will have demonstrated reliability in administration of the ADIS-C/P.

### Data completeness and monitoring

In our adult trials of Cognitive Therapy, data completeness has always been above 95%. Methods to enhance data completeness that we will adopt include the use of session-by-session outcome monitoring (so if someone drops out early the last available symptom measure can be used) and weekly outcome-measure informed supervision. As a phase I trial, a Data Management Committee was not considered to be necessary. As such, the trial team is responsible for monitoring and management of the data. Data will be monitored for completeness, consistency and plausibility by the trial statistician. The trial team and statistician will have full access to the final trial dataset. The study data will be reported in line with current CONSORT guidelines.

### Statistical analysis

All analyses will be intent-to-treat. No interim analyses are planned. Outcomes will be compared with hierarchical linear modelling. Time (midwait/midtreatment and postwait/posttreatment), treatment condition (OSCA, waitlist) and the time–condition interaction will be specified as categorical fixed factors, with baseline LSAS and gender as fixed covariates and participant as a random effect to account for between-person variation. Exploratory analyses using linear mixed effects models for each step to account for the nested data structure [43] will test for mediation of OSCA on social anxiety symptoms at posttreatment through candidate process variables from the cognitive model. Baseline outcomes will be included as predictors in all models. Categorical outcomes (response, remission, deterioration and diagnostic status) will be analysed using logistic regression, with treatment condition as the independent variable and baseline LSAS score and gender as covariates.

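### On its usual reading, the participant random effect forces equal variances at weeks 8 and 15, so the week-15 standard error is off if the spread changes; one extra covariance parameter removes the problem

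*Protocol article*

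**What the plan says.** In the protocol article, Statistical analysis opens with "Outcomes will be compared with hierarchical linear modelling". The two post-baseline visits, the condition and their interaction are categorical fixed factors. Baseline LSAS and gender are covariates, with "participant as a random effect to account for between-person variation". The section names no random slope, visit-specific residual variance or unstructured matrix. It also does not say which contrast from this model is the LSAS-CA-SR comparison. The Design section places the two visits at week 8 (mid-treatment or mid-wait) and week 15 (after treatment or wait). The Outcomes section makes change on the LSAS-CA-SR one of two primary outcomes, the other being recovery from the diagnosis.

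For the numbers analysed, Sample size states "Based on a conservative estimate of the effect of 1.0, we would need 17 per group for 80% power", inflated for dropout, "resulting in a final sample size of 40". On allocation, Recruitment and randomisation states "The ratio will be 1:1".

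**The concern.** A random intercept with one residual variance describes two visits with two parameters, so it cannot let the spread differ between them. The natural LSAS-CA-SR comparison is the difference between arms at week 15, and its standard error would borrow from the week-8 spread.

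There are two plausible reasons for the spread to grow. First, the model adjusts for baseline, and baseline usually predicts a later score less well than an earlier one. Second, response to therapy may vary between participants, and week 15 gives such differences more time to appear. The Background itself plans to look at who benefits most. If the spread does grow, the week-15 interval is too narrow and its p-value too small. If the spread shrinks, the error runs the other way and power is lost.

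**Working it through.** **Inputs.** From the article: two post-baseline visits, the fixed effects above, a participant random effect, 1:1 allocation, 17 per group before inflation and 40 in total. Assumed, because the article gives no figures: the standard deviations (SD) by visit, the correlation with baseline, the within-person correlation, and a two-sided 5% level.

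**The plan's own figure.** For a standardised effect of 1.0, the exact two-sample t-test has power 78.1% at 16 per group and 80.7% at 17, so 17 is right. Allowing 15% dropout, 34 / 0.85 = 40. The sample size stands. It serves here only to set the number per arm.

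**Step 1: what the model implies.** Let V8 and V15 be the baseline-adjusted variances and C their covariance. A random intercept (variance σb²) with one residual variance (σe²) gives V8 = V15 = σb² + σe².

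**Step 2: the week-15 standard error.** For each participant let s = (y8 + y15)/2 and d = y15 − y8, so y15 = s + d/2. The model treats s and d as independent. With complete, balanced data it therefore uses

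- Var(s) + Var(d)/4 = (V8 + V15 + 2C)/4 + (V8 + V15 − 2C)/4 = (V8 + V15)/2.

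The true value is V15. The difference is the omitted term Cov(s, d) = (V15 − V8)/2. With r = SD15/SD8:

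- both arms spread: k = SE(model)/SE(true) = √((1 + r²)/2) / r
- only the OSCA arm spreads: k = √((3 + r²) / (2(1 + r²)))

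The interaction depends on d alone and the average effect on s alone. The model estimates the variance of each freely, so neither contrast is distorted.

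**Step 3: a plausible r.** If the raw SD is constant and the correlation with baseline falls from 0.7 to 0.6, the adjusted SD goes from √(1 − 0.49) = 0.71 to √(1 − 0.36) = 0.80, so r = 1.12. A fall from 0.7 to 0.5 gives r = 1.21. The larger ratios below are assumptions without a stated source.

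**Step 4: type I error of the week-15 contrast**, approximately 2(1 − Φ(1.96k)):

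| SD week 8 → week 15 | r | k, both arms | error, both arms | k, OSCA only | error, OSCA only |
|---|---|---|---|---|---|
| 0.71 → 0.80 | 1.12 | 0.948 | 6.3% | 0.971 | 5.7% |
| 0.8 → 1.0 | 1.25 | 0.906 | 7.6% | 0.943 | 6.4% |
| 0.7 → 1.0 | 1.43 | 0.863 | 9.1% | 0.910 | 7.4% |
| 1.0 → 1.0 | 1.00 | 1.000 | 5.0% | 1.000 | 5.0% |
| 1.0 → 0.8 | 0.80 | 1.132 | 2.7% | – | – |

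With both arms spreading, the standard error is therefore about 5%, 9% and 14% too small in the first three rows, and 13% too large in the last.

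**Step 5: simulation.** At 17 per arm and within-person correlation 0.7, the random-intercept model gave 6.3%, 7.5% and 9.1% for growth in both arms, 5.7% to 7.5% for growth in the OSCA arm only, and 2.7% for the falling case. The unstructured model stayed at about 5%. The interaction kept its size (5.1% at 0.7 → 1.0).

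A separate simulation used 20 per arm, correlation 0.6 and the baseline and gender covariates. It gave these coverages of the nominal 95% week-15 interval:

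| r, both arms | random intercept | unstructured |
|---|---|---|
| 0.8 | 97.8% | 95.9% |
| 1.0 | 94.7% | 94.3% |
| 1.25 | 91.7% | 94.2% |
| 1.5 | 90.5% | 94.7% |

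The bias of the random-intercept estimate was at most 0.011 SD. At r = 1.0 the mean interval width was 1.29 SD (random intercept) against 1.30 SD (unstructured).

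**The case against.** The strongest reply is that the article never says the participant effect is the only covariance term. A random intercept with visit-specific residual variances also fits the sentence, and a condensed article commonly leaves residual structure to an analysis plan that is not shown here. This stands in part. The equal-variance model is the ordinary reading of the text, and the usual software default, but the text does not exclude a richer one.

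The second reply is that only one contrast is affected. This stands. A reader might infer that the whole LSAS-CA-SR analysis is invalid. The algebra above does not support that: the interaction and the average effect keep their error rate, and the diagnostic outcome has its own logistic regression. The article also does not name week 15 as the primary contrast, although it is the natural choice.

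The third reply is that the direction is assumed. A reader might infer that the 5% level will be exceeded. The documents contain no SDs by visit and so cannot show it; a falling spread makes the test conservative. Variation in response to therapy alone would act in the OSCA arm, where the inflation is smaller.

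The last reply is that, with a planned effect of 1.0 in a trial meant to give preliminary evidence, a standard error 5% too small would rarely change the conclusion. That is fair for the mildest case. It is no reason to keep a restriction that can be lifted at almost no cost.

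**Conclusion.** The point holds conditionally. On the ordinary reading, the stated model ties the week-15 standard error to the average of two variances that need not be equal. The possible error is moderate and confined to the standard error, interval and p-value of that one contrast; the point estimate is essentially unbiased.

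The sizes quoted rest on assumed SD ratios from 0.8 to 1.43, complete data and 17 per arm. Only the ratio of 1.12 follows from a stated mechanism, itself with assumed correlations. The documents do not support the firmer statement that the primary test is anti-conservative. They support only that it may be, and that the model as described gives no protection.

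**What to change.** Keep the stated fixed effects. Name the week-15 difference between arms as the LSAS-CA-SR comparison. Fit an unstructured 2x2 covariance for weeks 8 and 15, by REML with Kenward-Roger degrees of freedom.

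A participant random intercept with visit-specific residual variances gives the same model for positively correlated visits, as long as the covariance does not exceed the smaller of the two variances. Beyond that limit only the unstructured form fits freely, which makes it the simpler choice.

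The cost is a change of analysis wording and three covariance parameters instead of two. There is almost no loss of precision if the variances turn out equal, and no change to data collection, sample size or conduct. A baseline-by-time term is optional and not needed for this correction. If an analysis plan already specifies visit-specific variances, one sentence saying so closes the point.
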